#### Data monitoring

The NCI expressed high interest in having semi-annual data with respect to our primary outcome as the study was progressing. Thus, interim analyses are being performed every 6 months on our primary outcome and reported back to the NCI. As part of a data safety monitoring plan, at monthly study team meetings attended by all research study staff, the RA and CHWs present any adverse events that resulted from study participation as well complaints by participants and any other unanticipated harms and unintended effects of participating in the study. In addition, our quality control activities include monitoring of recruitment (weekly, using standard reports), monitoring the eligibility of enrolled participants, and periodic audit of consent forms to insure signatures and properly filed consents for all enrolled participants.

### Ethics and dissemination

#### Protocol approvals and amendments

The study was approved by the University of Miami Institutional Review Board, initial approval date on 12/22/2010, protocol #20100834. Since then, there have been eight approvals for minor amendments to the study protocol, most of which involve adding study personnel to the research team.

#### Consent

Informed consent is being obtained by our two bilingual RAs (Spanish/English, Haitian Kreyol/English) prior to the baseline intake. The women are given the informed consent form in their preferred language which they read and review along with the RA. If the woman states that she cannot read or if the CHWs suspects that the woman may not be able to read then all of the information in the consent form is read aloud to them. Once all questions have been answered, the woman is asked to sign the informed consent form. For women who cannot read, a witness signs indicating the form was read to the participant.

#### Confidentiality

To maintain participant confidentiality, study specific ID codes are used in all study tracking and analyses. Only the CHWs and project coordinator have access to the files linking participants with study ID numbers. These password protected files are stored in password protected computers. All paper surveys only have study ID numbers without names. These are stored in locked cabinets in locked offices.

#### Access to data

Only the study statistician has access to the raw data files entered by the data manager. Data files that have been cleaned and appropriately grouped and categorized will be made available to study personnel requesting such data. This includes the principal investigators, project coordinators, and our community partners. The statisticians will also make preliminary charts and tables when requested by study team members. Outside groups interested in access to the data will be granted access to limited datasets after submitting such requests to the study principal investigators.

#### Post-trial care

Ensuring that at the conclusion of the study all unscreened women are offered recommended screening was an important ethical consideration made by our community partners. Thus, once the study-related follow-up data has been collected, the CHWs will offer HPV testing to all women who have not been screened. For unscreened women declining the HPV testing, the CHWs will also offer their assistance in making appointments for Pap smears. For tracking purposes, we will also collect data on HPV outcomes among these women.

#### Dissemination policy

Our study findings will be presented at scientific meetings and published in peer reviewed journals. Based on our community-based participatory research framework, the active role of the community partners is such that we have agreed to have at least two partners play a key role in drafting each manuscript that will be published from this research effort and appropriately include them as authors in all such manuscripts. The NCI will also receive copies of our final results in our final report. Findings will also be reported in http://clinicaltrials.gov/. In addition, we will also present our results to community advisory boards we established in each community. We will also disseminate our findings to community members, patients, and other stakeholders, as well as in public forums, presentations to their boards, and lay summaries in the newsletters and ethnic media such as radio and television in all three languages (Spanish, Kryol, and English).

## Discussion

Minority immigrant women (both Hispanics and Blacks from Haiti) are less likely to be screened for cervical cancer than the general population. In this research project of the South Florida Center for the Reduction of Cancer Health Disparities (SUCCESS) we are conducting a randomized study on cervical cancer screening among 600 women in three underserved communities in Miami-Dade County. Data from this study will allow us to determine optimal approaches to increase cervical cancer screening among underserved women in our community. It will compare screening through standard public health outreach versus CHW-assisted patient navigation and a CHW intervention that includes the option for HPV self-sampling.

One methodological concern relates to our study design in which we have assigned one CHW to each community. As a result, the differences observed across different communities may reflect the impact of the CHW and not the intervention itself. Process data such phone calls, time with each participant, and follow-up will allow us to examine service intensity and examine if the intensity of the intervention varied in each community. In addition, as both groups two and three involve delivery of similar educational content, as a fidelity check of the CHW intervention we can examine differential changes in cervical cancer knowledge across the three sites. If present, such variations, may suggest differences in the CHW delivery of the intervention.

A second important methodological concern is that our primary outcome is a self-reported Pap smear, which is the approach used to track cervical cancer screening in national surveys such as the Behavioral Risk Factor Surveillance System and National Health Interview Survey. However, self-reports are a subjective measure and prior studies suggest that when initially asked about cervical cancer screening using self-reports, women may overestimate having a Pap smear by nearly 30 percentage points [29, 30]. However, those studies focused on women initially being asked and not those being assessed on a follow-up evaluation. For our study, we prioritized consistency in how our primary outcome was assessed initially and at 6-month follow-up. Further, in our study, women had many options where to obtain a Pap smear. These included FQHCs, public hospitals clinics, free clinics, Center for Disease Control-funded programs, and private providers. Obtaining access and querying the electronic medical records or manual chart review in each of these providers systems would have been administratively challenging. For these reason, we opted self-report as our primary outcome.

An additional concern relates to the evidence in support of HPV screening. Although HPV detection is gaining increased acceptance as a primary screening strategy, self-sampling has still not received full endorsement from the USPSTF. Instead, self-sampling is recommended as an option to be considered in hard-to-reach populations [28]. Having underserved women be screened through an intervention that has not been fully endorsed by the USPSTF raises issues of social justice and access to care inequities. The Affordable Care Act is an important step in helping improve access to care among many women. However, some low-income women residing in states that have opted not to expand Medicaid, such as Florida, and women who are undocumented will not benefit from the Affordable Care Act insurance expansions. Until all women have equitable access to care, the approach we propose is preferable to not having women screened. Additionally, our group continues to explore other approaches to expand cervical cancer screening. For example, we recently obtained an award from the National Cancer Institute to examine if HPV self-sampling kits distributed by CHWs at health fairs and mailed back are an effective screening option. Contributing towards the science of ensuring all women receive adequate cancer screening is an important contribution our SUCCESS center is making towards reducing and ultimately eliminating cancer inequities.

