#### Navigation

In addition to health education, a major role for the CHW is to offer women practical assistance that would facilitate her access to screening services. Navigation services may range from explanation of services offered at our participating clinical sites, availability of sliding fees and specific programs for cervical cancer screening for the uninsured (such as the Center for Disease Control early detection breast and cervical cancer screening programs), and assistance with making/scheduling the clinical appointments for the participant. On a case by case level, CHWs may provide assistance with other issues such as transportation (bus routes), potential language, cultural, or even child care issues, and, if requested, accompany the woman to screening appointments. CHWs also make appointment reminder calls the day prior. Within 2 weeks after a woman has the Pap smear screening, CHWs will contact the participant by phone to see if she requires any further assistance. If patients have not been notified of the results, with patient consent, the CHW tries to obtain the information from the FQHC and, with provider approval, may relay findings to the patients (all sites use electronic records). CHWs also play an important role by ensuring that each woman understands her test results. She may also provide further navigation by assisting with additional follow-up as needed, such as for colposcopy (available at each of our sites).

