#### Intervention Group 3: HPV self-sampling option

Women randomized to this arm receive the same health education session as Group 2. In addition, the education includes information on HPV self-sampling as an alternative screening method. They receive an offer of choosing between the HPV screening at the conclusion of the educational session or navigation services to a traditional Pap smear test at a local healthcare facility. If the woman chooses the HPV self-sampling strategy, the CHW provides detailed instructions to complete the sample collection. Using standardized operating procedures and study-specific visual aids and flipcharts we developed, they teach women the proper self-sampling collection technique. Women complete the test in a bathroom while the CHWs wait outside to answer any questions that may arise during the process.

We are using the HPV self-sampling device developed by Preventive Oncology International and the National Institutes of Health, which is a nylon swab 2 cm in diameter and 15 cm in length. Based on prior feedback on comfort and ease of use from earlier study participants, we are using the sampler without the outer sheath. After the woman collects the sample using the swab, she removes the swab out of her vagina and gives it to the CHW. The CHW puts the swab in a pre-labeled liquid media vial (ThinPrep, Holigic Inc., Bedford, MA, US) stirs the sample, caps the bottle, and stores the sample in a re-sealable plastic bag in a locked cabinet. Once a week, the CHW delivers the samples to the University of Miami’s Department of Pathology for processing. The sample is then sent to an outside CLIA approved laboratory (Quest Diagnostics Inc.) for HPV testing. Initially our specimens were being processed by Quest using the Cervista HPV Invader Assay (Holigic In.) [24]. This was later changed to APTIMA HPV Assay (GenProbe Inc.). The former tests for HPV using a DNA based two-step signal amplification method and the latter tests for mRNA using a three step transcription-mediated amplification assay [25]. Both assays test for the 14 HPV strains which have been identified as high risk HPV by the International Agency for Research on Cancer [26] (i.e., 16, 18, 31, 33, 35, 39, 45, 51, 52, 56, 58, 59, 66, 68). They have similar sensitivities for detection of cervical intra-epithelial neoplasia (CIN2+) [27].

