#### Primary outcome

The primary outcome is self-report of completion of a Pap smear or HPV test since the initial evaluation. We will assume that women who were lost to follow-up (no further contact) did not complete a cervical cancer screening. However, participants successfully contacted by phone but who declined in-person follow-up evaluation are asked if they completed a Pap smear or HPV test. Data obtained from this phone call will be included in a sensitivity analysis on our primary outcome.

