#### Sample size

In the study, we are recruiting 600 women from three study sites. The sample size was chosen to detect effects associated with a 20 point increase in the proportion of women screened in Group 2 (CHW) versus Group 1 (outreach) and an additional 15 percentage point increase in Group 3 (HPV self-sampling) versus Group 2. In addition, as women are randomized within each site, sample size calculations were adjusted to account for clustering of patients within each community. Based on these parameters, we examined power estimates under a variety of assumptions for attrition with estimates ranging from 0% to 30%. As shown in Figure 1, with a total sample size of 600 women (200 women in community), we will have sufficient power for the main study hypotheses, under a variety of attrition rate assumptions at a 0.05 level of significance.

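### Group 3 women whose HPV self-sample the trial holds count as unscreened if lost by month 6, and the one named sensitivity analysis does not use the specimens

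*Protocol article*

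**What the plan says.** The Primary outcome section defines the endpoint: "The primary outcome is self-report of completion of a Pap smear or HPV test since the initial evaluation". It then fixes the handling of loss: "We will assume that women who were lost to follow-up (no further contact) did not complete a cervical cancer screening". Statistical analysis repeats that assumption under intent-to-treat. The only sensitivity analysis named for this endpoint uses answers given by telephone by women who decline the in-person visit.

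The section on Intervention Group 3 describes how a self-sample travels. The woman gives the swab to the community health worker (CHW), who places it in a labelled vial and delivers it weekly to the university pathology department. "The sample is then sent to an outside CLIA approved laboratory".

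For Pap smears, the Navigation section is more limited. If a woman has not been told her result, and with her consent, "the CHW tries to obtain the information from the FQHC".

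The Discussion names self-report as a methodological concern and reports that "women may overestimate having a Pap smear by nearly 30 percentage points". It answers that "those studies focused on women initially being asked and not those being assessed on a follow-up evaluation", that consistency between baseline and follow-up was given priority, and that searching the records of many different providers would be hard to administer. Sample size plans for 20 points between Groups 2 and 1, and for "an additional 15 percentage point increase in Group 3 (HPV self-sampling) versus Group 2".

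**The concern.** For one arm and one type of test, the trial does not depend on the woman's memory or on reaching her again, because it has the specimen. The scoring rule ignores that. A Group 3 woman who self-sampled and then could not be found at month 6 receives an outcome that the trial's own material contradicts. The error runs one way, against Group 3, and falls on the comparison that tests the self-sampling option.

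The Discussion's practical argument against records concerns charts held by outside providers. It does not apply to specimens that pass through the study's own chain. Telephone answers cannot repair the problem either: they are self-report, and they come only from women who were reached.

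At stake is whether a smaller-than-planned Group 3 versus Group 2 difference reflects the intervention or the scoring of lost women. Separately, the cited over-reporting leaves a reader unsure how far the self-reported contrasts can be trusted.

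**Working it through.** **1. The plan's own figure.** Inputs from Sample size and the Figure 1 legend: 600 women, effects of 20 and 15 points, level 0.05, power 80% and 90%, attrition 0-30%. The text does not give the Group 1 rate, the clustering adjustment, the sidedness or the allocation ratio. I assumed 1:1:1, two-sided, no design effect, and a Group 1 rate of 10-50%.

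n per arm = [1.96·√(2p̄(1−p̄)) + z_β·√(pA(1−pA) + pB(1−pB))]² / (pA−pB)²

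- Group 2 at 40% and Group 3 at 55%, 80% power: 173 per arm, 519 in total. With 30% loss, 173/0.7 rounds up to 248 per arm, 744 in total.
- Across the assumed Group 1 rates, the 15-point contrast needs 363-519 in total at 80% power and 483-693 at 90%. With 30% loss it needs 519-744 at 80%.

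So 600 is plausible but cannot be reproduced exactly.

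**2. Documented completions scored as failures.** Let s be the share of Group 3 that self-samples and L the share lost. Both are assumed, although L lies within the attrition range that the plan considers. If loss is independent of sampling, the Group 3 rate falls by s × L.

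| s | L | s × L |
|---|---|---|
| 35% | 10% | 3.5 points |
| 35% | 30% | 10.5 points |
| 45% | 20% | 9.0 points |
| 45% | 30% | 13.5 points |

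If self-samplers are lost less often than others, use their own, smaller loss rate for L.

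**3. Effect on the contrast, under the rule and under the log.** Step 2 gives a loss from the Group 3 rate, not the net bias in the contrast, because the same rule also discards real but undocumented screening in Groups 1 and 2. Suppose loss is equal across arms and unrelated to screening, self-report is accurate in women who are reached, and the true Group 3 versus Group 2 difference is 15 points.

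- Rule as written: 15 × (1−L). For L of 10-30% this is 13.5 to 10.5 points, a shortfall of 1.5 to 4.5.
- Specimen log added: 15 × (1−L) + s × L.
- Example with true rates of 40% and 55%, L = 20%, s = 45%. Rule: 44 − 32 = 12 points. Log: (44 + 9) − 32 = 21 points.

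The true 15 lies between the two, so the results are informative as a pair.

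**4. Over-reporting.** If a share f of unscreened women report a test, the observed rate is p + (1−p)f. Assume 200 per arm, no attrition and Group 1 rates of 10-40%.

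- Equal f in all arms multiplies each difference by (1−f). At f = 0.30, 20 points become 14.0 and 15 become 10.5. Power falls from 98-99.9% to 80-84% (Group 2 versus 1) and from 85-90% to 56-71% (Group 3 versus 2).
- Unequal over-reporting with no true effect: an excess of 5, 10 or 15 points in one arm gives a significant result with probability 17-33%, 52-80% or 85-98%.

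**The case against.** The choice of self-report is disclosed and reasoned. The assessor is blinded and every arm is asked in the same way. Scoring lost women as unscreened is conservative for Group 3. Women who meet the CHW for an hour and give a specimen may also be easier to retain, which would shrink the figures in step 2. Using the log brings its own bias, because it recovers lost women in one arm only, and step 3 shows that it can overshoot. This stands, and it is why the log should not replace the primary count. It does not justify leaving the specimens out altogether.

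Three stronger readings are tempting, and the article does not support them.

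- A reader might set nearly 30 points beside 20 and 15 and infer that misreporting swamps the planned effects. The figure is a level of over-report for Pap smears at first questioning, not a difference between arms. Women who enter this trial have also already said, to the CHW and again to the research assistant, that they had no recent Pap smear. Nor does the article say whether 20 and 15 points are meant as true or as self-reported differences; if the latter, the dilution in step 4 is not an extra loss. Unequal reporting is possible, since women know their allocation and only Groups 2 and 3 receive CHW sessions, but its size is conjecture. Equally, the article gives no evidence that follow-up answers are more accurate than first answers.
- A reader might infer that the trial also holds records for navigated Pap smears. Navigation describes conditional retrieval with consent, and women could go to other providers.
- A reader might infer that no misclassification analysis is planned. This is a condensed article, and the full plan may contain one.

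**Conclusion.** The point holds for the specimens. As written, the scoring rule gives a value that the trial's own material contradicts for Group 3 women who self-sampled and were then lost. The number affected is 3.5 to 13.5 points of the Group 3 rate, assuming 35-45% self-sampling and 10-30% loss independent of sampling, and fewer if self-samplers are better retained. The net effect on the Group 3 versus Group 2 contrast is smaller if loss is similar across arms: 1.5 to 4.5 points of a true 15. It works against Group 3. The one named sensitivity analysis cannot show it, because telephone answers are self-report too.

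The over-reporting figure supports a check on robustness and no more. It does not show that either contrast is biased, and it is no reason to abandon blinded self-report as the primary measure.

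**What to change.** Keep blinded self-report, with lost women scored as unscreened, as the primary analysis. Add a pre-specified sensitivity analysis that counts an HPV self-sample as completed from the specimen or laboratory log, including for women lost to follow-up. Report it beside the primary result for Group 3 versus Group 2 and for Group 3 versus Group 1. Define which specimens count: state how samples with insufficient material are treated, and exclude those collected under the post-trial offer described in Post-trial care. State plainly that the log rescues lost women in Group 3 only, so ascertainment differs by arm and the result may favour Group 3.

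A tipping-point analysis can accompany it, with over-reporting varied from 0 to 30 points, both equal across arms and differing by up to 10 points. Any agreement check on Pap smears should be limited to those for which the CHW obtained information from the health center.

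The cost is analysis wording and modest programming, with no chart review and no new staff. Enrolment stood at 582 of 600, so analysis rules are what can still change. Because the primary outcome is analysed every 6 months for the funder, record the date of the addition and which interim results had been seen by then.

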## Trial status

As of May 9, 2014, we have enrolled 582 of our target 600 women into the study.

## Abbreviations

CAB: Community advisory board
CHW: Community health workers
FQHC: Federally qualified health center
HCN: Health Choice Network of Florida
HPV: Human papilloma virus
NCI: National Cancer Institute
PCR: Polymerase chain reaction
RA: Research assistants
SUCCESS: South Florida Center for the Reduction of Cancer Health Disparities
US: United States
USPSTF: Unites States Preventive Services Task Force.
